### Sample Size Calculation

As the World Health Organization QOL assessment instrument-Bref (WHOQOL-Bref) comprises multiple facets, the *retrospective data* will be analyzed using a multivariate analysis of covariance (MANCOVA). This technique is more powerful than a univariate analysis of variance, resulting in a required sample size of 135 patients giving a medium effect and power of 0.80. Previous research [26] indicates that the minimal clinically important difference (MCID) of the WHOQOL-Bref slightly varies across its domains. Table 1 shows for each domain the MCID and standard deviation. On the basis of these statistics, the Cohen *d* effect sizes were calculated and transformed via Cohen *f* to the *f*^2^ effect sizes required in the MANCOVA power analysis. It turns out that 138 participants are required to detect the average *f*^2^ of 0.061 with a power of 0.80, given a significance level of .05.

With regard to the *prospective data*, mixed linear modeling will be used. Power analysis is performed for a repeated measures design investigating the interaction between treatment and time. We assumed a significance level of .05 and a medium effect size of partial eta squared of 0.05 and an average correlation of 0.50 among the 5 repeated measurements. On the basis of this, we require 33 participants to test with a power of 0.80, whether the 3 treatment groups differ in their change in QOL over the follow-up time. When assuming an effect size similar to the MCID’s reported in the table above, 27 participants are required to detect the medium effect of *f*=0.248 with a power of 0.80.

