### Statistical Analysis

All analyses will be conducted using SPSS V24.0 (Statistical Package for Social Sciences, Chicago Illinois, USA). Frequencies and descriptive statistics will be calculated to provide an overview of the characteristics of the study population. Statistical test results will be considered significant at a level of *P*<.05.

Concerning the retrospective study, a MANCOVA will be done after correcting theoretically important covariates to assess the differences between treatment groups on the 4 WHOQOL-Bref domains and the general facet. For each type of treatment, a 1 sample *t* test will be performed for each WHOQOL-Bref scale to compare the QOL scores with reference data.

For both the retrospective and prospective studies, a logistic regression analysis will be performed on the outcome variables’ (1) need for reintervention (yes/no) and (2) for each complication (yes/no), assessing the effect of treatment after correcting for theoretically important covariates. With regard to hospital stay in days, a Kruskal-Wallis test will be performed with the group (type of treatment) and days in hospital. Analysis of covariance will be used to compare proximal versus distal SAE, thereby correcting the effect for theoretically important covariates. To confirm/find prognostic factors for failure of NOM, a logistic regression analysis will be performed if NOM is a failure quickly after treatment. Otherwise, a survival analysis will be performed.

Regarding the prospective study, to assess the differences between groups in their change in QOL over time, a linear mixed model analysis will be conducted. To answer our research question, we will focus on the interaction effect between measurement occasion and treatment group, while correcting for theoretically important covariates. For the repeated measures, an unstructured covariance matrix will be used. Item-level missing values will be imputed according to the guidelines of the questionnaires. Scale-level missing values will be handled directly through maximum likelihood estimation, because the mixed model procedure makes use of all available data for each participant over all time points.

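### The prospective power figure of 33 rests on an effect-size label that does not fit its formula, and both prospective figures (33 and 27) are for a sphericity F test, not the planned unstructured mixed model

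*Protocol article*

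**What the plan says.** In the Protocol article, Sample Size Calculation, the prospective part concerns the treatment-by-time interaction, that is, "whether the 3 treatment groups differ in their change in QOL over the follow-up time". The inputs are a 5% significance level, and "a medium effect size of partial eta squared of 0.05 and an average correlation of 0.50 among the 5 repeated measurements". The conclusion is "we require 33 participants to test with a power of 0.80". A second calculation replaces the effect with f = 0.248, taken from the MCID/SD values in Table 1, and gives 27 participants.

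Under Statistical Analysis, the same interaction is to be tested in a linear mixed model. There, "For the repeated measures, an unstructured covariance matrix will be used", and "Scale-level missing values will be handled directly through maximum likelihood estimation". The software named is SPSS V24.0. No degrees-of-freedom method is given.

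**The concern.** Two things do not fit together.

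- **The effect-size label.** For a within-patient effect, partial eta squared is SS_effect/(SS_effect + SS_within-error). The within-patient error variance is σ²(1 − ρ), so the correlation has already made the denominator smaller. Supplying ρ as a further input makes sense only if the effect is standardised by the between-patient SD.
- **The test.** A repeated-measures F test under sphericity has 4(N − 3) error degrees of freedom, which is 120 at N = 33. A test based on an unstructured 5 × 5 matrix has about N − 3 = 30. It therefore has less power and, without a small-sample correction, does not hold its nominal level.

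This interaction carries the primary quality-of-life question in the prospective cohort. The Discussion attributes large uncertainty from the small sample to the clinical and cost-effectiveness analyses, because the calculation was based on the primary objective. A reader will take the primary analysis to be adequately powered. If it is not, a null interaction may be read as similarity of the three treatments. If the level is inflated, a significant interaction may be spurious.

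**Working it through.** **Inputs** (Sample Size Calculation and Table 1): α = 0.05; k = 3 groups; m = 5 occasions; ρ = 0.50; partial η² = 0.05, so f² = 0.05/0.95 = 0.0526 and f = 0.229; second effect f = 0.248. **Assumed, because the article does not state them:** sphericity (ε = 1) for the power formula, equal groups, complete data, no covariates.

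**1. Reproducing the plan.** Noncentral F with df1 = (k − 1)(m − 1) = 8, df2 = 4(N − 3) and λ = f² × N × m/(1 − ρ) = 10 f² N.

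| Effect | N | λ | Power |
|---|---|---|---|
| f = 0.229 | 30 | 15.79 | 0.790 |
| f = 0.229 | 31 | 16.32 | 0.807 |
| f = 0.229 | 33 | 17.37 | 0.838 |
| f = 0.248 | 27 | 16.61 | 0.810 |

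Thirty-three is the first multiple of three with power above 0.80, and 27 comes out exactly. The two matches identify the method.

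**2. Partial η² = 0.05 in its ordinary sense.** The correlation does not enter again. The multiplier of f² is then 4(N − 3) or 4N, depending on convention.

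- N = 33: λ = 0.0526 × 120 = 6.32, power 0.353; or λ = 0.0526 × 132 = 6.95, power 0.388.
- Power 0.80 is reached at N = 77 (0.805) with 4(N − 3), or 78 in equal groups (0.811); with 4N it is reached at N = 74.

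Put the other way round, the plan's λ at N = 33 corresponds to an error-based f² of 0.526/4 = 0.132, which is a partial η² of 0.132/1.132 = 0.116.

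**3. The effect meant on the between-patient SD scale.** Then λ = 10 f² N is the right expression, ρ belongs in it, and the results in step 1 stand for a sphericity F test. The words partial eta squared are then a mislabel.

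**4. The planned model.** Simulation with complete data, three groups and five occasions, using an unstructured covariance matrix.

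Power of a test that truly holds 5%, with the plan's own λ:

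- N = 33, f = 0.229: about 0.74 to 0.80 (Wilks about 0.75 in the main run).
- N = 27, f = 0.248: about 0.70 to 0.75.

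The range reflects the pattern of group differences and the choice of test statistic. With f = 0.229, about 39 patients bring the Wilks test above 0.80 (0.845). On the error-based reading of step 2, the same test has power of about 0.30 at N = 33 and needs about 81 patients.

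Type I error of an uncorrected Wald F:

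| Estimation | N = 33 | N = 27 |
|---|---|---|
| REML, denominator df N − 3 | about 7.5% | about 8% |
| Full ML | about 11% | about 12 to 13% |

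Near N = 78 these fall to about 6% and 7%. An unequal 20/8/5 split at N = 33 changed little (7.2% and 10.7%).

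**The case against.** The strongest reply is that nothing was miscalculated. The formula is a standard one for a within-between interaction, and 33 and 27 both follow from it. The protocol applies it to f = 0.248, which comes from MCID/SD and is on the SD scale, where ρ is a proper input. On that scale 0.05 (f = 0.229) lies next to 0.248, and the protocol calls both medium. On the error-based reading, 0.05 would equal an SD-scale f of only 0.229 × √(4/10) = 0.145. That is 59% of 0.248, or about 0.71 points against the average MCID of 1.219. A mislabel is therefore quite plausible. This stands, and it means that power of 0.35 to 0.39 is a consequence of the wording and not an established fact about the study. It does not rescue the text, because the label and the formula still cannot both be right.

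It also stands that the maximum-likelihood phrase occurs in a sentence about missing scale scores and does not clearly choose full ML over REML for testing. The degrees-of-freedom method may be set out in an analysis plan not shown here. And 27 to 33 is the required number; the realised enrolment is not reported, and a larger cohort would have less inflation and more power.

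A reader might infer that the sample size is an arithmetic error, that neither 0.80 power nor the 5% level can hold, or that the cohort had to be more than twice as large. The documents do not support any of these. The arithmetic reproduces, the MCID-based 27 is not affected by the labelling point, and the size of the alpha inflation depends on choices the article does not state.

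**Conclusion.** The point holds in two parts.

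1. **Certain:** the effect size for the figure of 33 is misdescribed or misused. As written, the stated power of 0.80 is about 0.35 to 0.39, and 74 to 78 patients would be needed. If the label is at fault, the figure of 33 stands for the test it was computed for.
2. **Independent of that choice:** the test that was powered is not the test that is planned. On the reading most favourable to the plan, a valid unstructured test falls modestly short of 0.80 (about 0.74 to 0.80 at 33; 0.70 to 0.75 at 27). An uncorrected test at these sizes runs at about 7 to 8% with REML or 10 to 13% with full ML. An uncorrected test can exceed 0.80 power, but only by giving up the 5% level.

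The results in the second part assume complete questionnaires and no covariates; missing questionnaires over 12 months would lower power further. The inflation figures apply at N = 27 to 33 and shrink as N grows.

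**What to change.** State whether 0.05 is relative to within-patient error or to the between-patient SD, and correct the term or the calculation to match. Restate the prospective power for the unstructured model at the realised group sizes and questionnaire completion, preferably by simulation. Enrolment closed in December 2018, so this is a restatement and not a request for more patients.

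Test the occasion-by-treatment interaction with REML and a small-sample correction (Kenward-Roger, or an equivalent exact multivariate test where data are complete). If the named software version does not offer this, fit this one model in another package and say so.

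The cost is a few sentences, one simulation and possibly a second package for one model. The stated power will fall and p-values will be slightly larger.

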### Study Procedures

#### Retrospective Study

The clinical and imaging data of all splenic injury patients will be collected from the electronic patient files and registered anonymously. To measure QOL, all patients who are still alive will receive a written letter explaining the study, an informed consent form, the questionnaires, and a prestamped return envelope by mail. When a patient is willing to participate, he/she will sign the consent form and send it back in the return envelope, together with the completed questionnaires, assessing QOL and health status. When patients do not complete or return the questionnaires within 2 weeks, they receive a phone call as a reminder. When patients do not want to participate, the reason will be noted if the patient wants to let it be known. The patients who underwent SAE will be called for a voluntary single MRI abdomen at the ETZ Hospital in Tilburg.

This study has been reviewed and approved by the Medical Ethical Committee Brabant (METC Brabant, protocol number: NL54339.028.15) on January 27, 2016. The study has also been approved by the local ethical committee of the ETZ Hospital on February 9, 2016.

**Table 1 table1:** Minimal clinically important difference (MCID) per WHOQOL-Bref domain.

Domain	MCID	SD	Cohen *d*	Cohen *f*	Effect size *f*^2^
Physical	1.545	3.1	0.498	0.249	0.062
Psychological	1.259	2.5	0.504	0.252	0.063
Social	1.274	2.6	0.490	0.245	0.060
Environmental	1.142	2.3	0.497	0.248	0.062
General	0.876	1.8	0.487	0.243	0.059
Average	1.219	2.460	0.495	0.248	0.061

#### Prospective Study

In each participating hospital, an interventional radiologist and a trauma surgeon will be designated as principal investigators. Each hospital will also have a research assistant, most likely a radiology technologist or a member of the research team. The daily work will be carried out by the research assistant under the supervision of the principal investigator at the ETZ Hospital (CR). The research assistant will check daily whether potential eligible patients were admitted to the hospital. This will be done by checking the subscription list, verbally checking with the attending (resident) radiologist and trauma surgeon, and verifying the data in the electronic patient record. The subscription list will be placed at the dictation station of the radiologist, where the trauma diagnoses are reported. If a patient is treated for a traumatic spleen injury, baseline characteristics will be collected and he/she will be screened for the inclusion and exclusion criteria. The clinical data of all eligible patients will be collected anonymously in the database. As soon as the patient can talk and is lucid, the assistant will visit the patient to provide a verbal and written explanation about the study. The time for consideration of participation is 1 week. When a patient is willing to participate, he/she will sign a consent form. If not, the reason will be noted if the patient wants to let it be known. Each inclusion will be reported to the principal investigator (CR). Total follow-up time is 1 year after treatment with time points at 1 week and 1, 3, 6, and 12 months after treatment.

Patients will complete the questionnaires at all time points. The questionnaires of time point 1 will most likely be handed out to the patients at the hospital ward (intensive care, medium care, or general ward), usually by the research assistant of that hospital. At the other time points, patients will be sent an email to complete the questionnaires, assessing QOL, quality of care, health care consumption, and return back to work (if applicable). These questionnaires will be completed by the patient using a secure Web-based program: Data Management by Research Manager [27]. If a patient does not have internet, the questionnaires will be provided on paper with a prestamped return envelope. When patients do not complete or return the questionnaires within 2 weeks, they will receive a phone call as reminder. When patients no longer want to participate, the reason will be noted if they want to let it be known. Patients treated with SAE will receive an MRI abdomen 1 month and 1 year after treatment.

This study has been reviewed and approved by METC Brabant (protocol number: prospective study NL54542.028.16) on May 18, 2016. The study has also been approved by the local ethical committees of the ETZ Hospital (6-13-2016), Maasstad Hospital (7-28-2016), Erasmus MC (9-21-2016), Albert Schweitzer Hospital (10-31-2016), Amphia Hospital (2-23-2017), Leiden University Medical Center (10-17-2017), Amsterdam University Medical Center (VUmc) (1-11-2018), Hospital Medisch Spectrum Twente (1-25-2018), Radboud University Medical Center (5-3-2018), and Isala Hospital (5-17-2018).

### Data Collection

Data of the retrospective and prospective study will be recorded in a secure online database (Data Management by Research Manager, Health Solutions Deventer) [27]. In the prospective study, the database will be available to every research assistant. The program complies with the new legislation for collecting and processing personal data in medical scientific research: General Data Protection Regulation dated May 25, 2018.

#### Clinical Data

For both the retrospective and prospective study, data will be collected from the electronic patient records and trauma registry (Network Emergency Care Brabant). The trauma registry compiles prehospital and hospital data of all trauma patients admitted after presentation to the emergency department. Patients with splenic injury will be identified by the International Statistical Classification of Disease and Related Health Problems (ICD-10) and Abbreviated Injury Scale (AIS) diagnosis codes starting with S36.x and 5442, respectively.

The collected data concern the following: age, sex, systolic blood pressure, hemoglobin, Glasgow coma scale (at arrival), intubation (Yes/No), imaging (US and/or CT), grading spleen injury (American Association for the Surgery of Trauma; see Table 2)[28], type of treatment (NOM/SAE/splenectomy), complications, hospital stay (days), spleen in situ at discharge (Y/N), reinterventions (Y/N), rehospitalization (Y/N), and mortality.

**Table 2 table2:** American Association for the Surgery of Trauma spleen injury scaling (1994 Revision).

Grade^a^		Injury description
**I**		
	Hematoma	Subcapsular <10% of surface area
	Laceration	Capsular tear <1 cm parenchymal depth
**II**		
	Hematoma	Subcapsular 10%-50% of surface area; or intraparenchymal <5 cm in diameter
	Laceration	1-3 cm parenchymal depth, which does not involve a trabecular vessel
**III**		
	Hematoma	Subcapsular >50% of surface area or expanding; or ruptured subcapsular or parenchymal hematoma; or intraparenchymal hematoma >5 cm or expanding
	Laceration	>3 cm parenchymal depth or involving trabecular vessels
**IV**	
	Laceration	Involving segmental or hilar vessels producing major devascularization (>25% of the spleen)
**V**		
	Laceration	Completely shattered spleen
	Vascular	Hilar vascular injury with devascularized spleen

^a^Advance one grade for multiple injuries, up to grade III.

#### Questionnaires

Patients in the retrospective study will complete the questionnaires once. Patients in the prospective study will complete questionnaires at 1 week and 1, 3, 6, and 12 months after treatment (see Table 3).

##### World Health Organization Quality of Life Assessment Instrument-Bref

QOL will be assessed with the World Health Organization Quality of Life Assessment Instrument-Bref (WHOQOL-Bref) [29]. This 26-item questionnaire is a short version of the WHOQOL-100, and it assesses 4 domains (physical health, psychological health, social relationships, and environment) as well as 1 general facet, *Overall QOL and General Health*. The questions in the domains are derived from the 24 facets of the WHOQOL-100, with 1 item from each of the facets. Each item is rated on a 5-point rating scale. Higher scores indicate a better QOL [29,30]. The WHOQOL-Bref has good psychometric properties [30-33].

##### 12-Item Short-Form Health Survey

The 12-Item Short-Form Health Survey (SF-12) is a shorter version of the 36-Item Short-Form Health Survey (SF-36), which will be used for evaluating individual patients’ health status, researching the cost-effectiveness of a treatment, and monitoring and comparing disease burden. The SF-12 covers 8 domains: physical functioning, role limitations because of physical problems, bodily pain, general health, vitality, social functioning, role limitations because of emotional problems, and mental health [34,35]. From these domains, summary scores for the physical component (PCS) and mental component (MCS) can be computed. The 12 items for the SF-12 were selected such that the SF-12 component scores explain 90% of the variability in PCS and MCS scores of the SF-36 [34]. The SF-36 was used as a criterion for validation of the SF-12. The SF-12 and the SF-36 components and scales are scored with the algorithms specified by the developer [35]. The minimum possible score is 0 and the maximum possible score is 100. The SF-12 has good reliability and validity [36-42].

##### Euroqol 5-Dimensional 5-Level Questionnaire

The Euroqol 5-Dimensional 5-level questionnaire (EQ-5D-5L) is a generic health status instrument that measures health-related QOL [43]. The descriptive system of the instrument comprises 5 dimensions (mobility, self-care, usual activities, pain/discomfort, and anxiety/depression), which can be scored with 5 levels (ranging from no problems to severe problems). For the purpose of cost-effectiveness studies, health status is expressed in utilities, with a scale from 0 (death) to 1 (perfect health). The EQ-5D-5L can be used to derive utilities; the Dutch tariff can be used for this purpose [44]. Moreover, the EQ-5D-5L has good psychometric properties [45-50].

##### iMTA Productivity Cost Questionnaire

The impact of disease on the ability of a person to perform work should be part of an economic evaluation when a societal perspective is applied. The iMTA Productivity Cost Questionnaire (iPCQ) is a generic, nondisease-specific questionnaire, and it is applied in national and international studies [51]. The questionnaire is currently available in more than 10 languages, including Dutch. Both indirect cost because of absenteeism and the productivity losses because of presenteeism (ie, sick, but working) are taken into account. A manual is available, containing information on the modular structure of the iPCQ and its scoring and valuation methods that are used for cost calculations. By applying productivity costs, the answers of the iPCQ can be monetized and, as such, used in health economic evaluations.

**Table 3 table3:** Timeline of the prospective study concerning measurements.

Time point	Timing and setting	Demographics	Questionnaires	Imaging
T1	After treatment, during admission	Demographic factors and clinical data	Quality of life (WHOQOL-Bref^a^); health status (SF-12^b^); and health-related QOL^c^ (EQ-5D-5L^d^)	—^e^
T2	1 month after treatment, at home (MRI^f^: outpatient clinic)	—^g^	Quality of life (WHOQOL-Bref); health status (SF-12); health-related QOL (EQ-5D-5L); productivity costs (iPCQ^h^); and medical consumption (iMCQ^i^)	MRI (SAE^j^ patients only)
T3	3 months after treatment, at home	—^g^	Quality of life (WHOQOL-Bref); health status (SF-12); health-related QOL (EQ-5D-5L); productivity costs (iPCQ); and medical consumption (iMCQ)	—^e^
T4	6 months after treatment, at home	—^g^	Quality of life (WHOQOL-Bref); health status (SF-12); health-related QOL (EQ-5D-5L); productivity costs (iPCQ); and medical consumption (iMCQ)	—^e^
T5	1 year after treatment, at home (MRI: outpatient clinic)	Clinical data	Quality of life (WHOQOL-Bref); health status (SF-12); health-related QOL (EQ-5D-5L); productivity costs (iPCQ); and medical consumption (iMCQ)	MRI (SAE patients only)

^a^WHOQOL-Bref: World Health Organization Quality of Life assessment instrument-Bref.

^b^SF-12: 12-Item Short-Form Health Survey.

^c^QOL: quality of life.

^d^EQ-5D-5L: Euroqol 5-Dimensional 5-Level questionnaire.

^e^At this time point, no MRIs have been completed.

^f^MRI: magnetic resonance imaging.

^g^At this time point, no demographic or clinical data have been collected.

^h^iPCQ: iMTA Productivity Cost Questionnaire.

^i^iMCQ: iMTA Medical Consumption Questionnaire.

^j^SAE: splenic artery embolization.

